## Abstract

**Background:**

The majority of patients using antihypertensive medications fail to achieve their recommended target blood pressure. Poor daily adherence with medication regimens and a lack of persistence with medication use are two of the major reasons for failure to reach target blood pressure. There is no single intervention to improve adherence with antihypertensives that is consistently effective. Community pharmacists are in an ideal position to promote adherence to chronic medications. This study aims to test a specific intervention package that could be integrated into the community pharmacy workflow to enable pharmacists to improve patient adherence and/or persistence with antihypertensive medications - Hypertension Adherence Program in Pharmacy (HAPPY).

**Methods/Design:**

The HAPPY trial is a multi-centre prospective randomised controlled trial. Fifty-six pharmacies have been recruited from three Australian states. To identify potential patients, a software application (MedeMine CVD) extracted data from a community pharmacy dispensing software system (FRED Dispense^®^). The pharmacies have been randomised to either 'Pharmacist Care Group' (PCG) or 'Usual Care Group' (UCG). To check for 'Hawthorne effect' in the UCG, a third group of patients 'Hidden Control Group' (HCG) will be identified in the UCG pharmacies, which will be made known to the pharmacists at the end of six months. Each study group requires 182 patients. Data will be collected at baseline, three and six months in the PCG and at baseline and six months in the UCG. Changes in patient adherence and persistence at the end of six months will be measured using the self-reported Morisky score, the Tool for Adherence Behaviour Screening and medication refill data.

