### Pharmacy Eligibility Criteria

Pharmacies that met all the following criteria were eligible to participate in the HAPPY trial:

• use the pharmacy dispensing program 'FRED Dispense^®^';

• agree to install a software application (MedeMine CVD) to identify patients who are using or have used antihypertensive medicines in the previous six months;

• have at least 40 patients who are currently using or have used antihypertensive medicines in the previous six months;

• have a private counselling area within the pharmacy where one-on-one consultation with a patient will be shielded from the public eye and ear;

• willingness and ability to attend project training either face-to-face or online;

• have time within the working week to allocate about one uninterrupted hour per patient to collect the baseline data; and

• able to follow-up participants for at least six months from baseline.

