### Phase I

Phase I training was delivered to all participating pharmacists and included the project overview, patient recruitment including the use of MedeMine CVD software to identify patients using antihypertensive medications, calculation of MedsIndex score, use of BP monitors and collection of baseline data.

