### Sample size

Australian, European and North American studies have estimated that around 50% of patients initiating an antihypertensive medication discontinue their medication (become nonpersistent) within twelve months [22]. To demonstrate a 15% difference in adherence between the control and intervention groups at six months (e.g. 50% in the UCG versus 65% in the PCG) with 80% power and a two-sided p-value of 0.05, 182 patients are required per study group. To allow for potential drop-outs (approximately 25% over six months) 225 patients need to be recruited per group; i.e. a total of 450 patients at baseline.

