## Discussion

To our knowledge, HAPPY trial is the first RCT testing a comprehensive package of evidence-based interventions able to be integrated into the community pharmacy workflow, to enable pharmacists to improve patient adherence and/or persistence with antihypertensive medications. HAPPY trial is unique because we have taken into consideration the 'Hawthorne effect' in the UCG by having a third group of patients (HCG) who are taking or have taken antihypertensives in the previous six months but not included in the UCG. In addition, UCG pharmacists and their patient participants will not be disadvantaged as, after the study period is completed, they will be offered the intervention package tested in the PCG, a strategy that is expected to enhance participant retention.

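### No size or margin is set for the hidden-control comparison, so its planned difference test can check for a Hawthorne effect on refills but cannot show that the effect was controlled

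*Protocol article*

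**What the plan says.** The abstract (Methods/Design) describes the HCG as a third group found in the UCG pharmacies and disclosed to the pharmacists only at six months. The next sentence reads "Each study group requires 182 patients".

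The one derivation of that number is in Sample size: "To demonstrate a 15% difference in adherence between the control and intervention groups at six months", with the example "50% in the UCG versus 65% in the PCG", "with 80% power and a two-sided p-value of 0.05", and the result "182 patients are required per study group". The recruitment total there, 450, is twice 225 and so counts two groups; the HCG is neither sized nor counted.

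Cluster randomisation gives the HCG's purpose as a check on the effect of data collection in the UCG. Data analysis compares UCG and HCG on MedsIndex only, at six months, by a paired t-test and/or signed-rank test, and states no margin.

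Under Training, "Phase I training was delivered to all participating pharmacists". The adherence-focused Phase II reaches UCG pharmacists only after the six-month follow-up.

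The abstract's Discussion lists control of the Hawthorne effect as a unique feature. The main Discussion says "we have taken into consideration the 'Hawthorne effect' in the UCG by having a third group of patients (HCG".

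**The concern.** The article calls the HCG a check in two places and a form of control in the abstract's Discussion. A check by difference test supports control only if a null result rules out effects that matter, and that depends on a size or margin chosen for this contrast. None is given: the only number available was chosen to detect a treatment effect of 15 points.

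The contrast also has limited reach. UCG and HCG patients attend the same pharmacies, so any consequence of Phase I training or trial participation that touches all of a pharmacy's patients is common to both groups and drops out. And because only MedsIndex is compared, nothing is learned about the self-reported Morisky and TABS scores.

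At stake is a headline claim, not the primary comparison. A non-significant result could be taken to show that UCG patients behaved as in ordinary care, when a moderate effect of being observed would often go undetected.

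**Working it through.** **Inputs from the article:** 50% and 65%; two-sided 0.05; 80% power; 182 per group (Sample size and abstract). **Not in the article:** a MedsIndex SD, a Hawthorne effect size or a margin. The proportion figures below are therefore illustrative, with a 50% base rate and independent patients; the SD figures are scale-free.

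**1. Reproducing 182.** With mean proportion 0.575:

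n = [1.96·√(2·0.575·0.425) + 0.842·√(0.25 + 0.2275)]² / 0.15² = 169.3, rounded up to 170.

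Continuity correction: (169.3/4)·[1 + √(1 + 4/(169.3·0.15))]² = 182.4. So 182 is the continuity-corrected size for the PCG-UCG contrast and for nothing else.

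**2. Power of UCG v HCG at 182 each.** Power = Φ{[d√n − 1.96√(2p̄q̄)] / √(p₁q₁ + p₂q₂)}, no continuity correction:

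| True difference from 50% | Power | n per group for 80% |
|---|---|---|
| 5 points | 16% | 1,565 |
| 7.5 points | 30% | 693 |
| 10 points | 48% | 388 |
| 15 points | 83% | 170 |

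The difference detectable with 80% power is about 14.5 points.

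**3. What a null result leaves open.** 95% half-width = 1.96·√(2·0.25/182) = 0.103, or 10.3 points. An estimate of exactly zero gives about −10 to +10; 10.3/15 = 0.68, about two thirds of the treatment target. An equivalence test (two one-sided 5% tests, true difference zero) with a 10-point margin would have 21% power at 182 per group and would need 429 per group for 80%.

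**4. On the planned scale.** For a continuous score, (1.96 + 0.842)·√(2/182) = 0.29 SD is detectable with 80% power. Power is 16% for 0.1 SD and 48% for 0.2 SD.

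**5. Comparing within pharmacy.** This multiplies the variance by (1 − ICC). For assumed ICCs of 0.01 to 0.10, power for 10 points moves from 48% to between 49% and 53%: the right analysis, but a small gain.

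**6. More HCG records.** Assume 28 UCG pharmacies (half of 56) with 30 non-participants each: 40 antihypertensive users under Pharmacy Eligibility Criteria, less 10 recruits. That gives 840.

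Half-width = 1.96·√(0.25/182 + 0.25/840) = 0.080, or 8 points. Power becomes 23%, 45% and 69% for 5, 7.5 and 10 points, and the detectable effect is 2.80·√(1/182 + 1/840) = 0.23 SD. The 182 UCG patients are the limit.

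**The case against.** Several points on the other side stand.

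- **No cap on the HCG.** A reader might infer that it is held to 182. Nothing says so: the abstract states a requirement, its application to the HCG rests on sentence order, and Cluster randomisation defines the group simply as antihypertensive users who are not UCG participants. The supportable statement is that the HCG is not separately sized.
- **Same-pharmacy sampling is sensible for the stated target.** For an effect of data collection on patients it removes differences between pharmacies. A reader might call the UCG pharmacies trained in adherence, but they had Phase I only, and the HCG stays hidden from them until month six. Extra attention given only to known UCG participants would show in the contrast. Only pharmacy-wide effects are invisible.
- **The main comparison is largely protected.** A reader might infer that an undetected Hawthorne effect masks the intervention's benefit. Phase I training went to all pharmacists, and baseline and six-month measurements are made in both arms, so shared effects should largely cancel between PCG and UCG.
- **Enlarging the HCG has drawbacks.** Eligibility depends partly on a diagnosis confirmed through the GP, which a dispensing extract cannot supply. MedeMine preferentially picked out late or poor refillers, so adding every non-participant could make the groups less alike. The criterion "have at least 40 patients who are currently using or have used antihypertensive medicines in the previous six months" counts users, not eligible patients, and 7 to 10 recruits is a request to each pharmacist, so 840 is not a lower bound for comparable patients.
- **The full protocol may say more.** Power for an ancillary check is often left there. But the article itself names the test and makes the claim, and those can be judged as written.

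**Conclusion.** The point holds in a limited form. The 182 has no bearing on UCG v HCG beyond showing that effects about as large as the treatment target would probably be seen. A non-significant result would count against an effect near 15 points (83% power), so it would be too strong to say that the check supports nothing. It could not exclude an effect of up to about 10 points even if the estimate were zero, and it says nothing about effects shared by all patients of a pharmacy. The claim of control is stronger than the planned check.

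The point figures assume a 50% base rate, a binary measure and independent patients. The actual power for MedsIndex cannot be fixed without an SD; 0.29 SD is the corresponding scale-free figure. The intervals reflect sampling error only, since UCG and HCG were not randomised against each other.

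**What to change.** 1. **Data analysis.** Replace the paired test of UCG v HCG, which concerns two different sets of patients with no pairing described, by a pharmacy-stratified estimate of the six-month MedsIndex difference with its 95% confidence interval. State that non-significance will not be read as absence of an effect.
2. **Abstract and Discussion.** Describe the HCG as a check for a patient-level effect of data collection on refills, and limit any conclusion to the effects that the interval excludes.
3. **Optional.** Take more HCG records from UCG-pharmacy non-participants, chosen by the same MedeMine refill criteria as the invited patients. This needs no patient contact, but the ethics approval for HCG dispensing data must be confirmed to cover it. The gain is modest: under the assumptions above, the half-width falls from 10 to 8 points.

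The cost is a little more analysis and a slightly less favourable claim. The randomised comparison and patient recruitment are unchanged.

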**Discussion:**

To our knowledge, this is the first research testing a comprehensive package of evidence-based interventions that could be integrated into the community pharmacy workflow to enable pharmacists to improve patient adherence and/or persistence with antihypertensive medications. The unique features of the HAPPY trial include the use of MedeMine CVD to identify patients who could potentially benefit from the service, control for the 'Hawthorne effect' in the UCG and the offer of the intervention package at the end of six months to patients in the UCG, a strategy that is expected to improve retention.

**Trial Registration:**

Australian New Zealand Clinical Trial Registry ACTRN12609000705280

## Background

A continuous positive correlation exists between increasing blood pressure (BP) and mortality rates [1]. The cardiovascular mortality benefit associated with achieving BP control through medications has been demonstrated through large-scale clinical trials [2,3]. Unfortunately, the majority of patients on antihypertensive medications fail to achieve their recommended target BP [4-6]. Poor adherence with medication regimens and a lack of persistence with medication use are two of the major reasons for failure to reach target BP [6]. Several antihypertensive medication trials have found persistence after one year to be less than 50% [7-9]. On any day, patients who were still engaged with the drug dosing regimen omitted about 10% of the scheduled doses, of which 42% were of a single day's dose and 43% were part of a sequence of several days [7]. Adherence and persistence are likely to be much worse in routine clinical practice where, unlike clinical trials, patients' use of medications is not closely monitored.

There is no single intervention to improve adherence with antihypertensives that is consistently effective. Medication nonadherence is a multi-factorial issue. Interventions, either individually or in combination, for improving adherence with antihypertensives that have some evidence base are: simplifying dosing regimens, motivational strategies, unit dose packaging, educational counselling over the telephone, refill reminders, self-monitoring, and dose-tailoring [10-13]. As medicines experts in primary care, community pharmacists are in an ideal position to address adherence and persistence issues in people with hypertension. In a US study of 200 community-dwelling elderly patients, a 36% absolute increase in medication adherence followed a comprehensive pharmacist intervention with educational and structural components, which was also associated with improved cardiovascular outcomes [14]. The educational component included intensive and frequent counselling by a pharmacist, while the structural component involved packaging of medications in blister packs that contained each patient's daily medications. Australian community pharmacists are uniquely positioned in the healthcare system to undertake a role in cardiovascular medication management, a role supported by public opinion [15]. However, the pharmacist's role in addressing intentional and unintentional nonadherence to antihypertensive medicines in a sample of patients at risk of nonadherence remains untested using a randomised controlled design.

### Aim of the research

To test a specific intervention package that could be integrated into community pharmacy workflow to enable pharmacists to improve patient adherence and/or persistence with antihypertensive medications - Hypertension Adherence Program in Pharmacy (HAPPY).

### Primary outcome measures

The primary outcomes of the HAPPY trial are changes in patient adherence and persistence at the end of six months. These will be measured subjectively using the self-reported Morisky scale [16] and the Tool for Adherence Behaviour Screening (TABS) [17] and objectively using the medication refill data (e.g. MedsIndex score [18]). The Morisky scale assesses both intentional and unintentional nonadherence and comprises four items. Responses for each item are scored 0 for 'yes' and 1 for 'no' (except for the item 'are you always careful in taking medicines?' where the score was reversed) and added together. A total score of zero represents good adherence and a score of one or more represents suboptimal adherence. The TABS is another self-reported adherence measure, which was originally developed in Australian patients using chronic medicines. It has two subscales - 'adherence' and 'nonadherence' - each comprising four items to be answered on a 5-point Likert-type scale ('never' - 1 to 'always' - 5). The total score for 'nonadherence' will be subtracted from that of 'adherence'; a differential of ≥15 will be regarded as good adherence and ≤14 will be regarded as suboptimal adherence. The TABS measures both intentional and unintentional deviations from recommended management and has been shown to have greater incremental validity than other self-reported adherence measures [17]. The MedsIndex gives each patient a score out of 100 for each of their long-term medications, which is calculated based on their refill history. Any score less than 100 suggests suboptimal adherence.

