### Data analysis

Participant characteristics in the UCG and PCG will be compared at baseline. Paired t-tests and/or Wilcoxon Signed Rank test will be used to compare changes in total scores on the Morisky scale, TABS and MedsIndex between the PCG and the UCG at baseline and six months. MedsIndex scores will be compared using paired t-tests and/or Wilcoxon Signed Rank test in the UCG and the HCG at six months.

Baseline data will be used to identify factors associated with suboptimal adherence in the whole study population. Significant factors in univariate analysis (chi-square, Mann-Whitney U test and Student's t-test) will be further tested in multivariate analysis (linear regression) to identify independent predictors of nonadherence/nonpersistence in the study population. To adjust for cluster randomisation, a pharmacy variable will also be included in the multivariate models.

An economic evaluation will also be carried out and will be reported elsewhere.

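### The sample size powers one difference in the proportion adherent, on an unnamed instrument, but the planned arm comparisons use total scores on three unranked primary instruments

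*Protocol article*

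**What the plan says.** All references are to the Protocol article.

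- **Primary outcome measures.** "The primary outcomes of the HAPPY trial are changes in patient adherence and persistence at the end of six months". Two constructs are therefore primary. They are assessed with two self-report scales, Morisky and TABS, and with refill data, for which MedsIndex is given as an example. No instrument is placed ahead of the others. The section defines good and suboptimal adherence for each self-report scale: for Morisky, "A total score of zero represents good adherence and a score of one or more represents suboptimal adherence"; for TABS, "a differential of ≥15 will be regarded as good adherence and ≤14 will be regarded as suboptimal adherence". For MedsIndex, which is scored separately for each long-term medicine, anything below 100 counts as suboptimal.
- **Sample size.** The calculation is made "To demonstrate a 15% difference in adherence between the control and intervention groups at six months", with 50% v 65% as the example, 80% power, two-sided 0.05 and 182 per group. The instrument is not named. The only source offered for a 50% rate is the share of patients starting antihypertensives who stop within twelve months.
- **Data analysis.** Paired t-tests and/or Wilcoxon signed rank tests are to compare "changes in total scores on the Morisky scale, TABS and MedsIndex between the PCG and the UCG". Chi-square tests appear only in the screen of baseline factors, and nonpersistence appears only in the predictor model that follows that screen.

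**The concern.** The three sections do not describe the same primary hypothesis. One defines cut-offs, one powers a difference in a proportion, and one tests score changes in which the cut-offs play no part. A shift in a total score, or in MedsIndex points, cannot be set against a planned gain of 15 percentage points, so a positive or negative result would not answer the question for which the trial was sized.

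With three unranked instruments and two constructs, the plan also leaves open which result decides the trial. If that is settled after the data are seen, the nominal 5% error rate no longer describes the conclusion.

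**Working it through.** **Step 1. Reproduce 182.** Inputs from Sample size: p1 = 0.50, p2 = 0.65, d = 0.15, two-sided 0.05 (z = 1.960), 80% power (z = 0.8416). Mean proportion = 0.575.

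- Uncorrected: n = [1.960 × √(2 × 0.575 × 0.425) + 0.8416 × √(0.50 × 0.50 + 0.65 × 0.35)]² / 0.15² = (1.370 + 0.582)² / 0.0225 = 169.3, so 170.
- Continuity-corrected: n = (169.3 / 4) × [1 + √(1 + 4 / (169.3 × 0.15))]² = 182.4.

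This is 182 to the nearest integer and 183 rounded up. The stated figure is therefore a two-proportion calculation for one comparison at 0.05.

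**Step 2. Compare the sections.**

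| | Primary outcome measures | Sample size | Data analysis (between arms) |
|---|---|---|---|
| Construct | adherence and persistence | adherence; 50% rate drawn from nonpersistence | adherence scores |
| Instrument | three, unranked | not named | all three |
| Form | change; cut-offs defined | proportion at six months | change in total score |
| Time | six months | six months; source rate at twelve months | baseline and six months |

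No comparison between arms in the third column uses the cut-offs in the first or the proportion in the second. None is set out separately for persistence.

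**Step 3. What 182 per group gives for a score.** For a two-sample comparison of means at 80% power, the detectable standardised difference is (1.960 + 0.8416) × √(2/182) = 0.29 SD, before any allowance for clustering. The article gives no SD and no target difference for any of the three scores, so this cannot be turned into score points or set against the 15-point planning difference.

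**Step 4. Error rate if the three instruments stay co-equal.** Two assumptions are needed that the article does not state: each instrument is tested at two-sided 0.05, and any one can support a claim. The correlation between test statistics is also assumed.

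- Independent: 1 − 0.95³ = 14.3%.
- Simulation, 1,000,000 draws of three equally correlated normal statistics: 13.6% at 0.3, 12.5% at 0.5, 10.9% at 0.7 and 8.4% at 0.9.

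**Step 5. Cost of keeping all three with a Bonferroni split.** Each test is at 0.05/3 = 0.0167 (z = 2.394), with the same 50% v 65% for each.

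- Per group: 227 uncorrected, 240 continuity-corrected.
- Power per test at 182 per group, uncorrected: Φ[(0.15 × √182 − 2.394 × 0.699) / 0.691] = 69.4%. The same formula at 0.05 gives 82.8%.

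With one binary primary endpoint the 182 stands on this point. Whether it suffices under cluster randomisation is a separate question.

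**The case against.** The strongest reply is that a condensed article need not carry a testing hierarchy or multiplicity method, since these commonly sit in a statistical analysis plan, which is not shown here. That reply stands for multiplicity taken alone: the silence on adjustment is not a finding. It does not answer the mismatch, because the article itself says what was powered and what will be compared, and the two differ.

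A reader might infer several stronger things that the text does not support.

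- *Success on any one instrument at 0.05 is planned.* The level 0.05 appears once, in Sample size, and no rule for success is stated. The and/or in the aim concerns adherence and persistence, not instruments.
- *The error rate is 14.3%.* That needs independent statistics, the least plausible case for two self-reports of the same behaviour in the same patients.
- *Persistence is not analysed at all.* Nonpersistence appears in the baseline predictor model, and the outcome section says the listed tools measure both constructs. What is missing is a separate comparison of persistence between arms.
- *The three-month visit shows the primary result is collected by the treating pharmacist.* That visit is for the PCG only and is not the primary time point. Who administers the scales is in any case a different issue from endpoint choice.
- *Refill data are the obvious primary measure.* MedsIndex is scored per medicine, pharmacists are trained to calculate it, refill reminders are part of the intervention, and recruitment favours patients with poor refill adherence. Nothing shows that 50% v 65% is realistic at a cut-off of 100.

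**Conclusion.** The point holds as an inconsistency within the article. The powered hypothesis, a 15-point difference in the proportion adherent at six months, is tied to no instrument and has no stated test between arms. The tests that are stated have no derivable power. This conclusion needs no assumption beyond reading the three sections together.

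The multiplicity consequence is conditional. It is about 8% to 14% against a nominal 5%, if each instrument is tested at 0.05, if any one suffices, and for assumed correlations of 0.9 down to 0. It should be reported as what the wording leaves possible, not as what the investigators intend.

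This should be corrected. It decides what the trial can conclude, and it can be settled by wording.

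**What to change.** - Name one instrument and one patient-level definition of good adherence as the single primary endpoint, and state both in Primary outcome measures and in Sample size.
- Test the six-month proportion, PCG v UCG, at two-sided 0.05, in a model that allows for pharmacy clustering and adjusts for baseline adherence on that instrument. The Data analysis section has no such model for the outcome at present, so it must be written in.
- Make the other two instruments, the total-score changes and persistence secondary or supportive. Give persistence its own definition and comparison between arms.
- If the refill measure is chosen, define how scores on several medicines combine into one status per patient, and check that 50% v 65% is plausible at the chosen cut-off.
- Justify the 50% rate for the chosen instrument at six months, since the source cited concerns discontinuation within twelve months.

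The cost is protocol wording. Success could no longer be claimed on whichever instrument turns out favourable. Dichotomising discards some information, which the secondary score analyses retain. Keeping all three instruments primary would instead call for about 240 per group under a Bonferroni split, before any allowance for clustering or drop-out.

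### The Morisky item coding and its cut-off contradict each other, so the one total labelled good adherence cannot be reached by a patient who reports always being careful

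*Protocol article*

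**What the plan says.** All of the scoring is in the protocol article, Primary outcome measures. The Morisky scale is one of the instruments for the primary outcomes: "These will be measured subjectively using the self-reported Morisky scale [16] and the Tool for Adherence Behaviour Screening (TABS) [17", alongside refill data. On its structure: "The Morisky scale assesses both intentional and unintentional nonadherence and comprises four items". On the coding: "Responses for each item are scored 0 for 'yes' and 1 for 'no' (except for the item 'are you always careful in taking medicines", this last being the one item "where the score was reversed" before the four are summed. On classification: "A total score of zero represents good adherence and a score of one or more represents suboptimal adherence".

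The Data analysis section uses the sum of the items, not the two-way classification. The planned tests are to "compare changes in total scores on the Morisky scale, TABS and MedsIndex between the PCG and the UCG at baseline and six months".

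No other section gives a different coding or corrects this one.

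**The concern.** The coding and the cut-off point in opposite directions. The coding gives 1 for the adherent answer to the 'always careful' item, so a higher total goes with better adherence. The cut-off reserves the good label for the lowest possible total. Both are explicit statements about a primary measure, so this is not detail left to a fuller protocol or an analysis plan.

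Two uses are exposed. Any proportion of patients with good adherence on the Morisky scale would be counted from the wrong group. The planned comparison of changes in the total has no agreed direction: by the coding a rise is improvement, by the cut-off a rise is worsening.

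**Working it through.** **Inputs** (Primary outcome measures, except the last):
- Four yes/no items, each scored 0 or 1, so the total runs from 0 to 4 and there are 2^4 = 16 answer patterns.
- Coding: 'yes' = 0, 'no' = 1. The 'always careful' item is reversed: 'yes' = 1, 'no' = 0.
- Cut-off: 0 = good, 1 or more = suboptimal.
- Wording of the other three items: not printed. Assumption: 'yes' means nonadherence on each. The article supports this, since it describes a scale of nonadherence and reverses only the positively worded item.

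**Step 1, no assumption needed.** Take a patient who answers 'yes' to 'always careful'. That item contributes 1 and the other three contribute 0 or more, so the total is at least 1 and the label is suboptimal. This covers 2^3 = 8 of the 16 patterns, and none of them can be good. A total of 0 requires 'no' to that item. A fully adherent patient says 'yes' to it, so cannot be classed as good however the other three items are worded.

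**Step 2, with the assumption.** Each adherent answer scores 1 under the printed coding and each nonadherent answer scores 0. With k nonadherent answers the total is therefore 4 - k. Under the flipped coding ('yes' = 1, 'no' = 0, 'always careful' reversed) the total is k. Applying the printed cut-off to both:

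| Nonadherent answers (k) | Patterns | Total, printed coding | Label | Total, flipped coding | Label |
|---|---|---|---|---|---|
| 0 | 1 | 4 | suboptimal | 0 | good |
| 1 | 4 | 3 | suboptimal | 1 | suboptimal |
| 2 | 6 | 2 | suboptimal | 2 | suboptimal |
| 3 | 4 | 1 | suboptimal | 3 | suboptimal |
| 4 | 1 | 0 | good | 4 | suboptimal |

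Two patterns (k = 0 and k = 4) change label between the codings. The other 4 + 6 + 4 = 14 do not.

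**Step 3, the change score.** If T is the total under the printed coding, the flipped total is 4 - T. A change from baseline to six months becomes (4 - T6) - (4 - T0) = -(T6 - T0). Its size is the same and its sign is opposite.

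**The case against.** The strongest reply is that this is a slip in one sentence. Exchanging the 0 and the 1 in the coding makes everything consistent, the article is a condensed account, and neither the scoring sheet nor the data dictionary is shown. That is possible and the document cannot exclude it. It limits what can be said about the data, but it does not remove the contradiction in the stated rule.

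It can also be said that the planned analysis uses total scores. Under the printed coding the total is ordered coherently, in the same direction as the TABS differential and the MedsIndex score, where higher is better. Step 3 shows that flipping it leaves the size of a change, and a two-sided p-value, as they were. This stands. A wrong reading of direction arises only if someone scores as printed and then takes direction from the cut-off sentence.

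The total of 4 for a fully adherent patient rests on inferred item wording. That is fair, but Step 1 does not need the inference.

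A reader might go further in four ways that the document does not support:
- That the size of the error is 15 of 16 patterns labelled suboptimal. The same count holds under the flipped coding, because the cut-off always leaves exactly one good pattern.
- That the classification is wholly inverted. Only the two extremes exchange labels.
- That predictors of nonadherence would have reversed signs. The Data analysis section does not say which adherence measure is the dependent variable, or whether it is the total or the dichotomy. A uniform reversal would not follow from the dichotomy.
- That pharmacists have already mis-scored patients. The article says that they administer the scale, not that they compute or classify the total.

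**Conclusion.** The point holds as a contradiction between the coding and the cut-off of a primary measure. Without any assumption, answering 'yes' to the 'always careful' item rules out the good label. With the assumption that 'yes' means nonadherence on the other three items, the good category as written contains only fully nonadherent patients and excludes every fully adherent one.

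In answer patterns, the error is 2 of 16. How many patients that represents cannot be stated, because the article gives no distribution of Morisky scores. For the total score, what is at stake is the sign of the effect, not its size, and a rise would be read as worsening only if direction is taken from the cut-off. Any effect on the predictor models depends on whether the Morisky total or the dichotomy is used there. Whether the fault lies in the trial's scoring or only in the article's text is open.

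It should still be corrected before the measure is analysed, because following the printed rule gives a wrong classification.

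**What to change.** Make the coding and the cut-off agree in one of two ways:
- score 'yes' = 1 and 'no' = 0 with the 'always careful' item reversed ('yes' = 0, 'no' = 1), and keep 0 = good and 1-4 = suboptimal; or
- keep the printed coding and define 4 = good and 0-3 = suboptimal. The Morisky total then runs in the same direction as TABS and MedsIndex.

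State which direction of change in the total is improvement. Check the scoring sheet and the data dictionary against the chosen rule. Re-score from item-level answers only if the printed rule was actually applied.

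The cost is about one sentence in the protocol and an entry in the data dictionary, plus re-scoring if the check shows it is needed. No new data collection is required provided the item answers were kept.
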